### **10.9 Annual reporting by the sponsor to the Agency**

1.Regarding investigational medicinal products other than placebo, the sponsor shall submit annually through the database referred to in Article 10.5.1 to the Agency a report on the safety of each investigational medicinal product used in a clinical trial for which it is the sponsor.

2. In the case of a clinical trial involving the use of more than one investigational medicinal product, the sponsor may, if provided for in the protocol, submit a single safety report on all investigational medicinal products used in that clinical trial.

3. The annual report shall only contain aggregate and anonymised data.

4. The obligation referred to in paragraph 1 starts with the first authorisation of a clinical trial in accordance with this Regulation. It ends with the end of the last clinical trial conducted by the sponsor with the investigational medicinal product.

#### **10.10 Withdrawal of Study Participants**

The researchers may decide to withdraw the patient from the study if:

- The medical problem becomes worse.
- The researchers believe that participation in the research is no longer safe for the patient.
- The researchers believe that other treatment may be more helpful.
- The sponsor or the EMA stops the research for the safety of the participants.
- The sponsor cancels the research.
- The patient is unable to keep appointments or to follow the researcher's instructions.

#### **10.11 Pregnancy**

If a woman becomes pregnant during the course of this study, the patient will be excluded.

All medical decisions concerning her and her fetus will be in Multidisciplinary consultation meeting and will be presented thereafter.

- Reporting of pregnancy

Irrespective of the treatment received by the subject, any pregnancy occurring during the study must be reported immediately.

Pregnancies must be reported on the Sponsor Pregnancy form, which is sent to Sponsor pharmacovigilance (see contact details provided on the pregnancy form), and on the AE page in the e-CRF.

- Follow-up of pregnancy

Any pregnancy must be followed to its conclusion and its outcome must be reported to the Sponsor pharmacovigilance.

#### **10.12 Data safety monitoring board (DSMB)**

As Truxima is an approved EMEA and FDA treatment, we do not anticipate any impediments to patient enrollment or significant adverse or serious adverse events. As a result, no data safety advisory board is required during the study.

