## 2.2 Secondary Objectives

The following objectives are to compare between a personalized treatment of iMN driven by anti-PLA2R1 antibody epitope profiles and the GEMRITUX therapeutic protocol:

1. Complete clinical remissions at M6, M9, M12, M18, M24
2. Partial clinical remission at M6, M9, M12, M18, M24
3. Immunological remissions at M6, M9, M12, M18, M24
4. Proteinuria and albuminuria at M6, M9, M12, M18, M24
5. Changes in proteinuria and albuminuria from baseline at M6, M9, M12, M18, M24
6. Serum creatinine and estimated glomerular filtration rate (eGFR) at M6, M9, M12, M18
7. Changes in serum creatinine and eGFR from baseline at M6, M9, M12 and M18
8. PLA2R1-Ab titers at M6, M9, M12, M18 and M24
9. Recording all AEs/SAEs during study follow-up, 24 months

The following objectives aim to study risk factors for remission or relapse:

10. To determine risk factors for remission (immunological and clinical, partial or complete) at M12 in patients pooled from the two arms
11. To determine risk factors for relapse (between M12 and M24) in patient responders at M12, pooled from the two arms

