### Schedule of assessments

|                                          | M0 | M3                                | M6 | M9 | M12 | M18 | M24 |
|------------------------------------------|----|-----------------------------------|----|----|-----|-----|-----|
| Selection criteria                       | X  |                                   |    |    |     |     |     |
| Informed Consent                         | X  |                                   |    |    |     |     |     |
| Pregnancy test                           | X  | X                                 | X  | X  | X   |     |     |
| Randomisation                            | X  |                                   |    |    |     |     |     |
| Medical history and demographics         | X  |                                   |    |    |     |     |     |
| Weight, Edema, Blood pressure            | X  | X                                 | X  | X  | X   | X   | X   |
| Vaccination                              | X  |                                   |    |    |     |     |     |
| HBP Medications                          | X  | X                                 | X  | X  | X   | X   | X   |
| Serious adverse events treatment related | X  | X                                 | X  | X  | X   | X   | X   |
| Estimated GFR CKD EPI                    |    |                                   | X  | X  | X   | X   | X   |
| Urine analyses                           | X  | X                                 | X  | X  | X   | X   | X   |
| Blood sample b                | X  | X                                 | X  | X  | X   | X   | X   |
| PLA2R1-Ab                                | X  | X                                 | X  | X  | X   | X   | X   |
| Epitope Profile                          | X  | X                                 | X  | X  | X   | X   | X   |
| Residual Rituximabemia                   |    | X                                 | X  | X  | X   |     |     |
| Rituximab-Ab                             | X  | X                                 | X  | X  | X   |     |     |
| Cytokine profile                         | X  | X At first remission a |    |    |     |     |     |
| B and T cells count                      | X  | X                                 | X  | X  | X   | X   | X   |
| End of study                             |    |                                   |    |    |     |     | X   |

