### 10.3 Adverse Event Reporting

An adverse event is any condition that occurs after enrollment, whether or not considered related to study treatment. Signs and symptoms existing prior to study and documented on the baseline Medical History form or Physical Examination Form are not considered AEs. Only baseline signs and symptoms that worsen while the subject is on the study drug are considered adverse events.

At every visit, participant will be questioned regarding the occurrence and nature of any adverse experiences. If any signs, symptoms or the results of the laboratory tests indicate an adverse effect, the study physician should determine the severity (grade) of the AE and judge the relationship to the study treatment. In addition, if an adverse event necessitates medical care, appropriate care will be provided. Adverse events should be documented on the Adverse Event Report form, regardless of relationship to the study drugs. Notably, AEs thought to be due to treatment with the study drug are still reported as AEs in this study. The following information will be collected for all Adverse Events:

- Start and stop dates
- Severity (See the Severity Grading section below)
- Relationship to study drugs (See the Association with the Study Drug below )
- Action taken with study drugs
- Treatment for the AE and outcomes

The only circumstance in which an Adverse Event Report Form will not be filled out will be isolated lab value abnormalities of grade 1 severity.

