### **14. Independent data-monitoring committee**

The independent data monitoring committee is a consultative committee charged with advising the study sponsor on the benefit/risk ratio of the conduct of a clinical trial.

Its members, all competent in the conduct of clinical trials (pathology, methodology...) are not directly involved in the study.

The selection of its membership is made by the sponsor in collaboration with the coordinating investigator.

They are nominated by the sponsor and their term of office corresponds to the length of the study.

They undertake their duties voluntarily, and agree to respect the confidentiality of the study data.

The committee will receive all versions of the protocol, the annual safety report, and may be consulted at any time by the sponsor if a suspected unexpected severe adverse reaction or unwanted effect is particularly difficult to analyze, and/or if the data may change the apparent risk/benefit ratio during the course of the study.

The committee will analyze the data sent to it, and may demand additional information. It then makes a recommendation about the future of the study (continue, modify, halt etc).

The committee will meet annually.

Each associate investigator declaring one of the following events:

- commencement of supportive renal dialysis,
- or a non-fatal cardiovascular event: myocardial infarct, cerebrovascular accident, coronary or peripheral revascularization procedure, amputation, hospitalization for heart failure, cardiac arrest and resuscitation),
- or cardiovascular mortality,
- or non-cardiovascular mortality.

will complete a specific form and supply a hospital summary or consultation record that documents the event. These documents will be sent to the Nice DRCl, who will pass them to the independent data monitoring committee before each of its annual meetings.

If there is evidence that brings the safety of the study intervention into question is identified, the protocol may be suspended.

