### **Study coordination and the analyses of the results**

A 50% of Study Coordinator will be employed at the coordinating center for the duration of the study. His tasks will be to coordinate the study, collect and enter data onsite.

In all investigators' centers, one vacation per month clinical research assistant for each visit of patient will be dedicated for data collection and data entry.

A budget is dedicated:

- for the creation of the database, the data management and the statistical analyses performed by a data manager and a statistician,
- for the monitoring by a monitor,
- for the ethical and logistical follow-up by a project manager,
- for the data safety by a pharmacist.

For the data committee, a budget will be allocated to the 4 members for their participation (one committee by year).

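### Section 10.12 denies the monitoring committee that Sections 14 and 15 create and fund, and the protocol gives conflicting scopes for which adverse events are recorded and compared

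*Protocol*

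**What the plan says.** **Committee.** Section 10.12 reasons that, because the product is already approved, "we do not anticipate any impediments to patient enrollment or significant adverse or serious adverse events". It concludes: "As a result, no data safety advisory board is required during the study". Section 14 says the opposite: "The independent data monitoring committee is a consultative committee charged with advising the study sponsor on the benefit/risk ratio". It describes how members are appointed and which documents they receive, and lets the committee recommend continuing, modifying or halting. It adds: "The committee will meet annually". In Section 15, under study coordination, "a budget will be allocated to the 4 members for their participation (one committee by year".

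**Recording of events.** The schedule of assessments has one safety row, "Serious adverse events treatment related", ticked from M0 to M24, and no row for adverse events in general. The visit lists in 8.5 for M3 to M24 name serious adverse events without any relatedness limit and do not name non-serious ones. Objective 9 in Section 2.2 is "Recording all AEs/SAEs during study follow-up, 24 months". Section 10.3 has participants questioned at every visit and says: "Adverse events should be documented on the Adverse Event Report form, regardless of relationship to the study drugs". Only isolated grade 1 laboratory abnormalities are exempt. Section 10.5 requires all SAEs to be reported to the sponsor, and 10.7 exempts certain planned, elective or routine hospitalisations.

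**Comparison.** Evaluation criterion 9 in Section 3 defines severe infections as those leading to hospitalisation. Under objective 9, Section 12.3.2 compares between arms only the proportion of patients with at least one such infection, by Chi-square or Fisher's exact test.

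**The concern.** These are operative rules, and the answer to two basic questions depends on which page is read: whether the trial has independent safety oversight, and which harms are recorded.

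A sponsor team acting on 10.12 would convene no committee. A site working from the schedule table would enter only the SAEs it judged treatment related. The trial is open label and the arms differ in exposure by design. In the personalised arm, patients with CTLD1/7 activity start rituximab 5 to 14 days after randomisation, while control patients receive none before M6. Sections 10.2 and 10.4 tie causality to the investigational product, so a relatedness filter would probably work differently in the two arms.

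The protocol also says, under collective benefit in Section 5, that the personalised strategy should lower the risk of serious adverse events. The only between-arm safety test it plans does not address SAEs as a whole.

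**Working it through.** No stated figure is at issue, so the check is mainly a side-by-side reading.

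**1. Does a committee exist?**

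| Place | Statement |
|---|---|
| 10.12 | No board needed; no significant or serious events anticipated |
| 14 | Independent committee; advises on benefit/risk; annual; may recommend continue, modify or halt |
| 15 | Four members funded, one meeting a year |

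Nothing says that 10.12 and 14 concern different bodies. The Section 14 committee receives the annual safety report and may be consulted on difficult suspected reactions, so it does the work of a safety board. The statements cannot both stand.

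**2. Does the reason in 10.12 hold within the protocol?** Section 5 lists infusion-related reactions, infections and cardiovascular events as the most frequent serious reactions to rituximab. Section 10.8 lists death, dialysis, thrombosis and severe infection as expected from the disease. The premise that no serious events are anticipated conflicts with both.

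**3. Which events are recorded?**

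| Place | Scope |
|---|---|
| Schedule of assessments | Treatment-related SAEs |
| 8.5, visits M3 to M24 | SAEs, no relatedness limit |
| 10.5 | All SAEs (10.7 exemptions apart) |
| 2.2, objective 9 | All AEs and SAEs, 24 months |
| 10.3 | All AEs whatever the relationship |

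There are three scopes: related SAEs, all SAEs, and all AEs. The schedule row is the narrowest and the only one with a causality filter.

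**4. Do objective, criterion and test match?** The objective covers all AEs and SAEs. The criterion and the test cover infections leading to hospitalisation. By the definition in 10.1, hospitalisation makes an event serious, so the tested events are a subset of SAEs. The rest of objective 9 has no matching criterion or test.

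**5. What could the schedule label do if it were followed?** Let r be the true SAE rate, equal in both arms, and let f and g be the shares judged related in the personalised and control arms. The captured rates are r × f and r × g, so the apparent risk ratio is f/g. The protocol gives no values for f or g; those below are assumptions.

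| r | f | g | Captured, personalised | Captured, control | Apparent ratio (true 1.0) |
|---|---|---|---|---|---|
| 20% | 80% | 40% | 16% | 8% | 2.0 |
| 20% | 60% | 30% | 12% | 6% | 2.0 |
| 20% | equal | equal | equal | equal | 1.0 |

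If 10.3 and 10.5 are followed, f and g play no part and this mechanism does not arise.

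**The case against.** The strongest reply is that these are wording conflicts and that the rest of the protocol already secures what matters. Most of that stands.

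- **Oversight is contradicted, not undefined.** A reader might infer from 10.12 that oversight has no content. Section 14 gives remit, membership, inputs, frequency and outputs, and lets the committee ask for more information.
- **Control-arm complications are not shown to be missed.** A reader might infer that thrombosis, severe infection or dialysis during delayed treatment would go unrecorded. Section 14 requires a specific form for dialysis, listed cardiovascular events and every death, whatever the cause. Criterion 9 counts severe infections without a relatedness limit. A thrombosis leading to hospitalisation is an SAE that 10.5 requires to be reported. Section 10.11 also refers to an AE page in the e-CRF.
- **The label does not plainly exclude controls.** The summary's account of study conduct counts symptomatic therapy as treatment, and 10.8 lists expected events for the antihypertensives, diuretics and statins.
- **Early exposure does not measure bias.** One can compute 64/2 = 32 patients per arm, 0.70 × 32 = 22.4 patients with CTLD1/7 activity (share from Section 7.1), and 22.4 × 0.5 year = 11.2 rituximab patient-years before M6, against none in controls. That describes the design under any recording rule. It counts no missed event.
- **Some detail belongs elsewhere.** AE tabulations, splits by period and the content of committee reports can be left to a statistical analysis plan or charter, which is not shown here.

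What remains is that the protocol contradicts itself on the committee, on the scope of recording, and between an objective and its own criterion. A later plan cannot settle which of two conflicting protocol rules the sites should follow.

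**Conclusion.** The point holds as three internal inconsistencies:

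1. Section 10.12 contradicts Sections 14 and 15 on whether a monitoring committee exists, and its stated reason conflicts with Sections 5 and 10.8.
2. The schedule row limited to treatment-related SAEs conflicts with the visit lists, objective 9, 10.3 and 10.5.
3. Objective 9 is wider than criterion 9 and the test in 12.3.2.

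The risk to the safety comparison is conditional. It arises only if sites follow the schedule label against 8.5, 10.3 and 10.5, and only if the share of events judged related differs between arms. Open-label causality assessment and the absence of rituximab in controls before M6 make that plausible, but the documents do not establish it and its size cannot be derived from them. The ratio of 2.0 in the illustration follows from assumed shares, and equal shares give 1.0. The planned severe-infection comparison carries no relatedness limit and is well defined. The primary endpoint, its test and the sample size are unaffected. This is a should-fix consistency correction.

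**What to change.** - **Section 10.12:** delete the statement that no board is required, together with its reasoning, and refer to Section 14.
- **Schedule of assessments and 8.5:** change the safety row and the visit lists to all adverse events and serious adverse events, whatever the causality, in line with 10.3 and 10.5. The exemptions in 10.3 and 10.7 can stay.
- **Objective 9, criterion 9 and 12.3.2:** align them by keeping the severe-infection comparison and adding a between-arm comparison of patients with at least one SAE, using the Chi-square or Fisher's exact test already named there.

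The cost is a wording amendment and, if the e-CRF mirrors the schedule label, one changed form item. The committee is already budgeted and 10.3 already requires all adverse events to be recorded, so no new visits, samples or patients are needed.

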### **11. Data collection**

#### **11.1 Study records**

A case report form (CRF) will be specifically designed for study data collection. The Clinical Research Assistant responsible for the sponsorship of the study, and the Data Manager of the Department of Clinical Research and Innovation at Nice will design the CRF, in coordination with, and under the responsibility of, the principal investigator.

#### **11.2 Database**

The study data will be recorded in the electronic record (e-CRF). This will be implemented by the Data Manager of the Department of Clinical Research and Innovation using RedCap® software from the finalized paper CRF. Parameter specification and the implementation of the e-CRF for data collection, including users training, will be the responsibility of the Department of Clinical Research and Innovation.

The investigators, together with the clinical research assistants, in each center will take responsibility for data collection and entering it directly into the e-CRF. The data will be securely stored, with specific access rights granted to members of the study team according to their role.

#### **11.3 Data quality control**

Data quality control will be performed on the e-CRF, using the patient medical file, by the sponsor during the planned monitoring visits by the Department of Clinical Research and Innovation's Clinical Research Officer.

Once the final data have been entered, checks for their validity and coherence will be performed by the Data Manager of the Department of Clinical Research and Innovation and requests for

verification issued. Throughout the study any modifications to the database will be recorded, enabling a full audit trail.

At the end of the quality control process, the database will be frozen and signed off by the principal investigator, the data manager and the head of biometric department at the Department of Clinical Research and Innovation. No modification of the data will be possible after this time.

The frozen database, together with the data management report, will then be transferred to the statistician for analysis.

## **12. Statistical analysis**

### **12.1 Analysis strategy**

The statistical analyses will be performed by the biostatistician of the Delegation of Clinical Research and Innovation (DRCI) at the Nice center.

Before each analysis is performed, the conditions for the application of the tests that were used will be verified. The various tests will be considered significant at a threshold of 5% (unless otherwise specified). Continuous variables will be described using the number of observations (N), arithmetic mean (Mean), standard deviation, minimum (MIN), median (Median), and maximum (MAX) values. Categorical variables will be summarized by absolute (N) and relative frequencies (%). The statistical analysis will be performed using SAS Enterprise Guide 5.1 software (Copyright (c) 2012 by SAS Institute Inc., Cary, NC, USA). The statistical analysis will be performed using SAS Enterprise Guide 5.1 software (Copyright (c) 2012 by SAS Institute Inc., Cary, NC, USA).

Population analyzed:

The study patients will be analyzed according to the intention to treat principle (ITT). Each patient will be analyzed as a part of the group to which he or she was assigned at randomization.

A *per protocol* analysis will also be performed, though the results of this analysis cannot be substituted for those of the intention to treat analysis.

Missing data:

The “last observation carried forward” (LOCF) strategy will be used to impute the missing data for the principal objective and, when possible, for the secondary objectives.

Disposition of patients:

According to the CONSORT 2010 statements, a flow diagram of the progress through the phases (enrollment, allocation, follow-up, and analysis) of this study will be presented. The number of screening failures and reasons for screening failures will be summarized. The characteristics of patients lost to follow-up over the course of the study will be reported.

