#### 1.4 MN recurrences

The rate of iMN recurrences after rituximab infusion is about 30% (32). MN recurrences are associated with rise in PLA2R1-Ab titers (9, 32). In our cohorts (Nice cohort + GEMRITUX), 7 patients out of the 34 who reached remission relapsed. MN recurrences after rituximab were associated with the appearance of anti-rituximab antibodies at month 6 ( $p=0.02$ ) and higher PLA2R1-Ab titer at month-3 and month-6 ( $p=0.04$  and  $0.03$  respectively). In competition assays, anti-rituximab antibodies could block in vitro complement and cell dependent rituximab cytotoxicity on B-cells. Inhibition of rituximab activity could favor the persistence of pathogenic memory B-cells and induce disease relapse, with an early reconstitution of the B-cell compartment (36). We will monitor serum rituximab levels at month 3 and month-6, anti-rituximab antibodies at month-3 and month-6 as well as at inclusion for relapsing patients, and B-cell compartments (transitional, mature/naïve, memory) at Month 0, Month 3, Month 6, Month 12 and Month 18 after rituximab infusion to correlate the appearance of anti-rituximab antibodies and the re-emergence of the memory B-cell with MN recurrences in an ancillary study.

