#### **8.4 Frequency of follow-up visit-protocol**

After randomization, all patients will be scheduled at M3, M6, M9, M12, M18 and M24 post-treatment for a routine follow-up, and benefit from a symptomatic antihypertensive and antiproteinuric treatment throughout the study period according to the KDIGO guidelines.

In the GEMRITUX group: at M6, if the patient exhibits an active disease (UPCR remains  $> 3.5$  g/g and albuminemia  $< 30$  g/l), they will receive two 375 mg/m^2 rituximab infusions at 1-week interval.

In the personalized group, rituximab injections should be scheduled between 5 and 14 days after randomization in case the epitope results are in favor for immunosuppressive treatment, as follows:

- at M0 and M6, if the patient exhibits anti-PLA2R1 anti-CTLD1 or CTLD7 activity, they will receive two 1 g infusions at 2-week interval.
- At M6, if a patient has an active disease/ anti-PLA2R1 ab + or if he has an active disease /anti-PLA2R1 Ab –, symptomatic treatment should be optimized. And if he exhibits anti-CysR restricted activity with active disease (UPCR remains  $> 3.5$  g/g and albuminemia  $< 30$  g/l), they will receive two 375-mg/m^2 rituximab infusions at 1-week interval.

[figure not shown]

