### **At the first relapse**

If the patient presents a still active disease with anti-PLA2R1 and anti-rituximab activity, the following cares are left to the investigator's discretion due to the Rituximab contraindication. However, the patient must perform the following visits according to the protocol.

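### LOCF for the month-12 primary endpoint scores patients last seen by month 6 before any rituximab in the control arm, but mostly after rituximab in the personalized arm

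*Protocol*

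**What the plan says.** Section 12.1 commits to an intention-to-treat analysis and fixes the missing-data method: the LOCF "strategy will be used to impute the missing data for the principal objective and, when possible, for the secondary objectives". The principal criterion is clinical remission, partial or complete, at M12. Section 12.3.1 compares it between arms by chi-square, or by Fisher's exact test in small samples.

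Treatment timing differs by arm (sections 8.4 and 8.5):

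- **Control:** "In the GEMRITUX group: at M6, if the patient exhibits an active disease", rituximab follows, 5 to 14 days after that visit. No control patient receives it earlier.
- **Personalized, CTLD1/7 activity (about 70%, section 7.1):** rituximab starts 5 to 14 days after randomization.
- **Personalized, CysR-restricted (about 30%):** symptomatic treatment to M6, as in the control arm.

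On withdrawal, section 10.10 says "The researchers may decide to withdraw the patient from the study if" any of several conditions applies, including "The medical problem becomes worse" and "The researchers believe that other treatment may be more helpful". Section 10.11 excludes a patient who becomes pregnant. By contrast, for patients with active disease and anti-rituximab antibodies at first relapse, section 8 adds: "However, the patient must perform the following visits according to the protocol".

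**The concern.** The trial asks whether remission at M12 differs between two complete strategies. The control strategy includes rituximab after M6 for patients whose disease is still active. A control patient last seen at M3 or M6 is scored under LOCF as though that half of the strategy did not exist. A personalized-arm patient lost at the same time has, in about seven cases out of ten, already been treated. The imputed values therefore compare symptomatic treatment with early rituximab, and this favours the experimental arm whenever the true M12 difference is smaller than the M6 difference. At stake is the type I error of the primary test in a trial of about 32 patients per arm.

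Section 10.10 is a separate weakness. It permits removal from the study, not only from study treatment, at the discretion of open-label investigators. That creates M12 gaps which continued follow-up would avoid, and it sits badly with the intention-to-treat commitment.

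**Working it through.** **Plan's own figure.** The protocol gives no figure for the effect of LOCF, but its sample size sets the scale. For 80% versus 45%, two-sided 5% and 80% power (section 7.2 prints α as 0.20 and β as 0.05; I read them as interchanged, since 12.1 tests at 5%):

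n = [1.960·√(2·0.625·0.375) + 0.842·√(0.80·0.20 + 0.45·0.55)]² / 0.35² = 28.8, so 29 per group. Then 58 × 1.1 = 63.8, so 64 in total, or 32 per arm. This reproduces the plan with an uncorrected two-proportion formula.

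**Inputs for M6 status (section 1.3).** Remission at M6: CysR-restricted under symptomatic treatment 43–50%; CTLD1/7 under symptomatic treatment 0.05–17%; CTLD1/7 after high-dose rituximab 64%. Weights are 30/70 (section 7.1).

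**M6 status by arm.**

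- Personalized: 0.3 × (43 to 50%) + 0.7 × 64% = 57.7 to 59.8%.
- Control: 0.3 × (43 to 50%) + 0.7 × (0.05 to 17%) = 12.9 to 26.9%.
- The CysR term is the same in both arms and cancels. The gap is 0.7 × (64% − 17%) = 32.9 points to 0.7 × (64% − 0.05%) = 44.8 points.

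As a cross-check, section 1.1 reports 21.1% remission after 6 months of symptomatic treatment alone in the earlier trial, inside the control range.

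**Effect of LOCF.** Let d be the fraction lost, equal by arm and all last seen at M6 (assumptions), with those lost having the M6 rates above. The expected difference is (1 − d) × (M12 difference) + d × (M6 gap), so the bias is d × (M6 gap − M12 difference).

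With equal true M12 rates (45% or 62.5% in both arms), by exact enumeration at 32 per arm and a nominal 5%:

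| Loss | False difference | Chi-square type I error | Fisher type I error |
|---|---|---|---|
| 0% | 0 | 5.4–5.9% | 2.9–3.2% |
| 10% | 3.3–4.5 points | 6.4–7.5% | 3.6–4.3% |
| 20% | 6.6–9.0 points | 9.2–12.4% | 5.5–7.8% |

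Counting missing as non-remission gives no false difference under the same assumptions; its chi-square error is 5.3–6.0% and its Fisher error 2.9–3.3%.

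**At the planning rates.** With a true difference of 35 points and 10% loss, LOCF gives 0.9 × 35 + 0.1 × (32.9 to 44.8) = 34.8 to 36.0 points.

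**Power at 10% loss, planning rates, 32 per arm.**

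| Handling | Rates | Chi-square | Fisher |
|---|---|---|---|
| Complete data | 80% vs 45% | 85% | 78% |
| LOCF | about 78% vs 42–43% | 84–87% | 77–80% |
| Missing = non-remission | 0.9 × 80% = 72% vs 0.9 × 45% = 40.5% | 76% | 67% |

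**Unequal loss (assumed: 20% control, 5% personalized; true rate 62.5% in both arms).** Missing = non-remission gives 0.95 × 62.5% − 0.80 × 62.5% = 9.4 points in favour of the personalized arm. LOCF gives 7.0 to 9.7. Neither rule protects against unequal loss.

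**The case against.** The strongest reply is that the effect is small where the protocol expects to be. Section 7.2 anticipates 10% loss and calls it minor. At that level Fisher's test, named in the sample-size calculation, stays below 5%, and under the planning rates LOCF is nearly unbiased. The asymmetry also ends once M9 is observed, because control patients with active disease at M6 have been treated by then. The 45-point end of the range rests on a printed 0.05% that looks very low for the cohorts described. All of this stands, and it limits the severity. It does not remove the point: type I error concerns the null, section 12.3.1 names chi-square first, and 10% is an expectation rather than a limit.

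Two stronger readings are tempting, and the protocol does not support either.

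- A reader might infer that section 10.10 drives the bias by removing worsening patients. Withdrawal there is discretionary. A patient withdrawn for worsening will mostly carry forward non-remission, which scores the same under LOCF as under a non-remission rule. The biased values come chiefly from treatment timing.
- A reader might infer that LOCF inflates success by carrying forward remissions that later relapse, since section 1.4 puts recurrence after rituximab at about 30%. That figure has no M6-to-M12 window, and section 3 defines relapse only after remission at M12. Section 1.3 shows remissions accumulating after M6, so on the planning rates carrying M6 status forward understates both arms.

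It is also fair to object that non-remission imputation is not neutral. The unequal-loss example shows this, so it must not be adopted alone.

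**Conclusion.** The point holds for patients last seen at M3 or M6, and should be fixed. LOCF is an explicit choice for the primary endpoint, and its direction is predictable: it favours the personalized arm whenever the true M12 difference is below the 33 to 45 points that treatment timing produces at M6. Under equal true M12 rates the distortion is modest at the planned 10% loss and material at 20%, where even Fisher's test exceeds 5%. These sizes assume equal loss by arm, every loss last seen at M6, lost patients following the protocol's M6 rates, and 32 per arm. Earlier or later last visits would change them. The withdrawal wording in 10.10 is a related but separate defect: it produces avoidable missing outcomes and is not the main source of the LOCF bias.

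**What to change.** - **Section 12.1:** for the primary endpoint, replace LOCF with the rule that a patient without an M12 remission assessment counts as not in remission. Name a sensitivity analysis for unequal loss: multiple imputation by arm and epitope profile, or a tipping-point table over the missing outcomes in each arm.
- **Sections 10.10 and 10.11:** state that leaving study treatment, for whatever reason, does not end outcome follow-up, and that M12 and M24 data are still collected unless consent is withdrawn. Section 8 already keeps one relapse subgroup on the visit schedule, so this is feasible.

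The two changes belong together. The non-remission rule is biased if loss differs by arm, and only retention reduces that risk.

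The drafting and programming effort is small. The real cost is power at the planning rates with 10% loss: about 76% by chi-square or 67% by Fisher, against 84–87% or 77–80% with LOCF. The sponsor should state this openly; each M12 assessment kept through better follow-up recovers part of it.
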